#### *Data collection procedures*

Procedures related to completion of the psychosocial assessment and baseline questionnaire are described in Procedures. Women will complete the psychosocial assessment on a single occasion. The content and order of individual questions in the e-version of the instruments will be identical to the paper-based version. Women select responses by touching the screen. If a woman does not answer a question, she will be prompted to respond before she can proceed. This is to mimic the usual screening process where the nurse would ask the woman to respond to a missing answer. A ‘SUBMIT’ button at the bottom of the baseline questionnaire will allow women to submit their responses.

The order of material on the tablet will be: (1) Participant Information Letter and Consent; (2) preamble describing the importance of screening and the follow-up with the healthcare provider; (3) ALPHA and EPDS; (4) the CAE, DES, and questions related to acceptability, feasibility, and disclosure; and (5) baseline questionnaire. The content of the baseline questionnaire includes questions that represent factors associated with prenatal mental health or disclosure of mental health concerns, and includes: (1) demographics (age, parity, marital status, education, income, ethnicity, country of birth, and length of time in Canada); (2) obstetrical history (current and past, including use of fertility treatments); (3) mental health history (diagnoses, treatment); (4) level of comfort with technology (for example, laptop, tablet); (5) quality of relationship with perinatal care provider; (6) level of social support, experience of talking with doctor/nurse/midwife about emotional health; and (7) adverse childhood experiences (using ACES questionnaire [48]). With the exception of the ACES (http://acestudy.org/ace_score), questions were derived from the All Our Babies longitudinal birth cohort study (http://www.prehot.org/The%20All%20Our%20Babies%20Study/) and the Maternity Experiences Survey (http://www.phac-aspc.gc.ca/rhs-ssg/survey-eng.php). Participants are required to answer all fields except for income, thus limiting the issue of missing data. Data for the economic evaluation will be collected from program accounts for technology and software costs, and by interviewing clinic staff to estimate clinic operation costs for the two alternatives. We will use a healthcare perspective and all costs will be shown in 2014 values.

No data will be stored on the tablets. When women ‘submit’ their information it will be sent to a secure server housed in the Faculty of Medicine & Dentistry’s Data Centre at the University of Alberta. The psychosocial assessment and questionnaire were built using an existing infrastructure offered by Checkbox Survey software provided by Women’s and Children’s Health Research Institute’s (WCHRI) Clinical Research Informatics. Data transfer between the tablet and server will be encrypted. Data imported to statistical databases for analysis will not be identifiable.

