#### *The control group*

Women in the control group will complete paper-based versions of the ALPHA and EPDS. Usual prenatal care at our clinic recruitment sites involves women self-completing the ALPHA on a single occasion during pregnancy, typically while they wait for their first or second prenatal visit. At the hospital recruitment site, usual care does not include formal screening, although women’s mental health status is monitored due to the high medical risk. Paper-based screening was chosen as the comparator because the primary objective of the study is to assess feasibility and acceptability of the electronic administration of a psychosocial assessment.

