#### *Procedures*

##### 

**Maternity clinics** At the maternity clinic recruitment sites, each eligible woman will complete the ALPHA and EPDS while they wait for their prenatal appointment - either via computer tablet or paper. After randomization to the control group, a message appears on the tablet, directing women to complete the ALPHA and EPDS on paper. An automatic ‘skip’ procedure ensures that the electronic versions of the ALPHA and EPDS are bypassed for women in the control group. Following completion of the paper-based psychosocial assessment, women will proceed to complete the baseline questionnaire on the tablet. Women in the intervention group will be directed to answer questions about emotional health (ALPHA and EPDS) and the baseline questionnaire on the tablet. All questions require responses, and thus women cannot proceed past questions with missing answers until completed. In keeping with the current clinic processes of including the assessment in the medical record, the electronic copy will be printed following completion. As is usual care in the maternity clinics, a Registered Nurse will review the assessment, judge whether women are at low, some, or high risk, discuss women’s psychosocial assessment responses with them, and provide follow-up referrals for those with some or high psychosocial risk with a mental health nurse affiliated with the clinic.

##### 

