**Hospital-based antenatal unit** In the antenatal unit, the research assistant will meet with women who have agreed to a follow-up contact by the research team. The research assistant will provide the tablet, a copy of the paper-based questionnaire, and an opaque envelope. The research assistant will be available to answer questions related to study participation, but then will leave the room to allow the woman to proceed to the computer randomization, and complete the assessment and baseline questionnaire independently. Thus, the research assistant will have no knowledge of the woman’s group assignment. Following randomization to the intervention group, women will be directed by a computer message to complete the ALPHA and EPDS on the tablet as well as the baseline questionnaire. Women assigned to the control group will be directed by a computer message to complete the ALPHA and EPDS on paper and then return to the tablet for completion of the baseline questionnaire. An automatic ‘skip’ procedure ensures that the electronic versions of the ALPHA and EPDS are bypassed for women in the control group.

In both cases, prior to the final submission of the baseline questionnaire, intervention and control group women will be prompted to place the paper-version questionnaire in the opaque envelope and seal it.

In the antenatal unit setting, procedures to maintain blinding of the research assistant are required because he/she will be both recruiting women and conducting the follow-up diagnostic interview. Blinding of the research assistant is maintained by: (1) distributing an opaque envelope and a paper-based version of the ALPHA and EPDS to all participants prior to randomization; (2) using a computer-based randomization process that reveals the assignment to the woman, but not the research assistant; (3) instructing all women to return the paper-based assessments to the envelope prior to giving the tablet and envelope back to the research assistant (an electronic message on the tablet prompts women to return the paper-based assessment to the envelope); and (4) training the research assistant to return all envelopes (unopened) to the research coordinator.

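### At the antenatal unit the tablet enforces an answer to every ALPHA and EPDS item and paper does not, so completion is partly mixed with mode in the secondary detection and psychometric comparisons

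*Protocol article*

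**What the plan says.** **Tablet.** Procedures, under Maternity clinics, states: "All questions require responses, and thus women cannot proceed past questions with missing answers until completed". Data collection procedures repeats the rule in general terms: "If a woman does not answer a question, she will be prompted to respond before she can proceed". It then gives the reason: "This is to mimic the usual screening process where the nurse would ask the woman to respond to a missing answer".

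**Paper.** Under The control group: "Women in the control group will complete paper-based versions of the ALPHA and EPDS". What happens to the paper form differs by setting.

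- Maternity clinics: "As is usual care in the maternity clinics, a Registered Nurse will review the assessment, judge whether women are at low, some, or high risk". The nurse also discusses the answers with the woman.
- Antenatal unit: "At the hospital recruitment site, usual care does not include formal screening". The research assistant leaves the room. Before the final submission women are "prompted to place the paper-version questionnaire in the opaque envelope and seal it". Blinding is protected by "training the research assistant to return all envelopes (unopened) to the research coordinator".

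The only other stated check on paper forms is a manual one by the research coordinator, on 30 control participants at three points in the study. Its purpose is to confirm that the paper version was the one used. No retrieval of blank items is mentioned.

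**Outcomes that use these forms.** The detection outcomes are EPDS total of 13 or more, EPDS anxiety subscale of 4 or more, and some or high risk on the ALPHA. The analysis is by chi-square, and Table 1 hypothesises higher proportions on the tablet. Sensitivity, specificity and predictive values are also compared between modalities.

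**The concern.** The trial sets out to compare electronic with paper administration of the same instruments. If one arm cannot skip an item and the other can, a difference in the proportion above a cutoff may reflect completeness rather than what women disclose in each mode. The EPDS is a sum score. A blank either lowers the sum, if scored 0, or removes the woman from a complete-case analysis. The difference is built into procedures that follow allocation, so randomisation does not balance it, and no later analysis can recover an answer that was never requested.

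The plan regards the tablet prompt as equivalent to a nurse's query. That is reasonable in the clinics. At the antenatal unit no such query is described, and the sealed envelope rules one out at the bedside. What is at stake is the reading of the secondary detection result and of the paper-versus-tablet psychometrics.

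**Working it through.** **Inputs from the article.** Inflow is 50 women per month in the clinics and 45 on the antenatal unit (Feasibility of achieving sample size). Symptom prevalence is 15% to 25% (Abstract). Allocation is 1:1 and the significance level is 0.05. The article gives no rate of blank paper items, so every loss rate below is an assumption.

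**Stated sample size, used below as n per arm.** n = 0.85 × 0.15 × (1.96/0.05)² = 195.92, rounded to 196. Then 196/(1 − 0.25) = 261.3, stated as 261. It reproduces.

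**Hospital share.** 45/(50 + 45) = 0.474. This is inflow; the enrolled split by site is not given.

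**Gap if only hospital paper forms lose true positives.** Gap = base rate × loss × 0.474, with no true effect of mode. The last column is the chance of a significant two-sided comparison of proportions at 261 per arm (normal approximation, 5% if there is no gap).

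| Loss of paper true positives in hospital | Gap at 20% base rate | Chance of significance |
|---|---|---|
| 10% | 0.20 × 0.10 × 0.474 = 0.9 points | 6% |
| 20% | 0.20 × 0.20 × 0.474 = 1.9 points | 8.5% |
| 30% | 0.20 × 0.30 × 0.474 = 2.8 points | 13% |

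The gap is proportional to the base rate in hospital: 0.7 to 2.1 points at 15%, and 1.2 to 3.6 points at 25%. The plan says that medically high-risk women have higher rates. At an assumed 40% in hospital the gap would be 1.9 to 5.7 points.

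**Does the direction always hold?** Let a share *a* of symptomatic women and *b* of other women leave a blank, and drop incomplete forms. The change in the positive rate among the affected women is 0.20(1 − a)/[0.20(1 − a) + 0.80(1 − b)] − 0.20. Take *a* from 10% to 30% and *b* from 5% to 10%.

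- a = b = 10%: 0.18/(0.18 + 0.72) − 0.20 = 0.
- a = 30%, b = 5%: 0.14/(0.14 + 0.76) − 0.20 = −4.4 points.

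The range is 0 to 4.4 points among the women affected, so the sign depends on symptomatic women skipping more often.

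**Does the scoring rule matter?** A 10-item, 0 to 3 scale was simulated (alpha 0.85, true rate at or above 13 of 15.2%), with blanks in the whole paper arm.

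| Blanks per item | Scored 0 | Complete case | Prorated |
|---|---|---|---|
| Random 2% | 14.5% | 15.2% | 15.1% |
| Random 5% | 13.5% | 15.3% | 14.9% |
| Random 10% | 11.7% | 15.1% | 14.5% |
| 1/2/5/10% by true item score 0/1/2/3 | 13.4% | 11.8% | 14.4% |
| 2/4/10/20% by true item score 0/1/2/3 | 11.5% | 8.9% | 13.5% |

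Paper detection is lower or about unchanged, never clearly higher. Restricted to hospital, each shortfall shrinks by roughly the factor 0.474.

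**The case against.** The strongest reply is that the article's rationale refers to usual screening, which exists only in the clinics. On that reading the sentence is accurate as far as it goes and makes no claim about the hospital. In the clinics the plan describes a nurse who reviews the form, discusses it and asks about gaps. That stands, and it confines the point to the antenatal unit. The tablet rule, however, applies at both settings, and no other reason for it is given.

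A second reply is that enforced completion belongs to e-screening as delivered. This is a legitimate choice of what to estimate. The article does not make it: it presents the prompt as matching what already happens on paper.

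A reader might infer more than the documents support:

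- *That the bias always favours the tablet.* It does not under random blanks with complete-case scoring, and a woman obliged to answer may choose a denying response.
- *That the primary outcome is biased.* The CAE and acceptability questions are answered on the tablet by both arms with responses required. Carry-over from compulsory ALPHA and EPDS items is conceivable, but nothing in the article sizes it.
- *That the hospital forms are never read.* They are unopened only as far as the research assistant is concerned. They go to the research coordinator, and the EPDS must be scored at some stage.
- *That the article claims complete paper data.* The statement that all fields but income are required follows the description of the baseline questionnaire, which both arms complete on the tablet.
- *That the tablet offers no way to decline an item.* A response is required, but the full list of response options is not shown.

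The sum-score mechanism also fits the EPDS better than the ALPHA, whose risk category is a judgement by a trained provider.

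**Conclusion.** The point holds for the antenatal unit. There, completion is enforced on the tablet, and on paper no step to query blanks is stated. Mode and completion are therefore partly mixed in the secondary detection comparison and in the psychometric comparison by modality. In the clinics the nurse review reduces the asymmetry to a difference in timing and in who prompts.

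The likely direction is lower paper detection, which is the hypothesised direction. It is conditional on blanks being scored 0 or being commoner in symptomatic women. The 0.9 to 2.8 points rests on an assumed loss of 10% to 30% of true positives, a 20% base rate, and enrolment in proportion to inflow. None of these is fixed by the article, and the true blank rate may be close to nil. Severity is low.

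**What to change.** 1. Extend the existing tablet message to control women. When they return to the tablet, and in hospital before the envelope is sealed, ask them to check that every question on the paper ALPHA and EPDS has an answer. Shown on the tablet to control women while the research assistant is out of the room, this leaves blinding intact.
2. Report item non-response by arm and site beside the detection results.
3. Limit the stated rationale for compulsory answers to the clinics.

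The cost is one added message line, one descriptive table and one edited sentence. A reminder is weaker than enforced completion, so some asymmetry may remain; the non-response table would show how much.

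Adding a decline option to each EPDS item would equalise the arms in another way, but it is not recommended. It alters a scored instrument with established cutoffs and invites missing items in both arms, at the expense of the psychometric objective.

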### Analysis

#### *Primary outcome and description of sample*

Intention-to-treat analysis will be conducted for all analyses. We will use descriptive data (frequencies/95% CI; means/standard deviation) to describe the sample. Baseline differences in groups will be compared using independent t-tests (means) and chi-square tests (%) to determine the extent to which randomization was successful. Statistical significance for all analyses is set at *P* <0.05. We will use two-tailed independent t-tests to compare intervention and control group differences in mean scores of the CAE and chi-square tests to compare proportions of women in each group responding affirmatively to questions on feasibility and acceptability.

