There is a clear need for a rigorous evaluation of the feasibility, acceptability, and psychometric performance of e-screening for prenatal mental health difficulties. A key consideration for evaluation is to determine whether established assessment tools are valid and reliable for use when delivered online. For example, it has been shown that some tools have different psychometric properties when delivered online, suggesting a need for different cutoff points [44]. Another key issue is the inclusion of women experiencing a broad range of degrees of psychosocial risk. Pregnant women with high-risk pregnancies represent a vulnerable group in that the prevalence of mental health problems in this group is more than three times greater than medically low-risk women [45,46]; however, medically high-risk women are rarely included in intervention studies of perinatal mental health.

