#### *Recruitment procedures, consent, randomization, and allocation procedures*

Recruitment procedures are similar across sites. Trained staff at the recruitment sites will use a standardized script to determine each eligible (see Eligibility criteria) woman’s interest in study participation. Women will be referred to an onsite research assistant who will provide the tablet. Women will complete the consent electronically on the tablet and receive the automatically generated copy via email. The research assistant will be available to answer questions about study participation and tablet logistics. A simple, computer-generated randomization process designed by the Women’s and Children’s Health Research Institute (WCHRI) at the University of Alberta allocates women (1:1 ratio) automatically to the control or intervention group, and they will receive a ‘pop-up’ message informing them that they will complete questions about emotional health on paper (control group) or tablet (intervention group). Computerized randomization preserves allocation concealment and reduces the possibility of selection bias since the research assistant is kept unaware of the group assignments until after the participants are allocated to groups.

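### Baseline items collected after allocation are significance-tested to judge the randomization, and setting, a strong prognostic factor known beforehand, enters neither the randomization nor the main between-arm tests

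*Protocol article*

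**What the plan says.** **Baseline tests.** Under Analysis, Primary outcome and description of sample, the protocol article states: "Baseline differences in groups will be compared using independent t-tests (means) and chi-square tests (%) to determine the extent to which randomization was successful".

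**Timing.** Under Recruitment procedures, women consent on the tablet and are then allocated automatically. Data collection procedures gives the tablet order after the consent and preamble as "3) ALPHA and EPDS; (4) the CAE, DES, and questions related to acceptability, feasibility, and disclosure; and (5) baseline questionnaire". The Procedures section agrees for control women. At the clinics: "Following completion of the paper-based psychosocial assessment, women will proceed to complete the baseline questionnaire on the tablet". On the antenatal unit they are told to "complete the ALPHA and EPDS on paper and then return to the tablet for completion of the baseline questionnaire". The baseline content includes demographics, obstetric history, mental health history, "level of comfort with technology (for example, laptop, tablet", relationship with the care provider, and adverse childhood experiences (ACES).

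**Randomization and setting.** Allocation is by "A simple, computer-generated randomization process" in a 1:1 ratio, with no stratification described. Women come from maternity clinics and an inpatient high-risk unit. The Background says of high-risk pregnancies that "the prevalence of mental health problems in this group is more than three times greater than medically low-risk women", and the Setting section repeats that their depression and anxiety rates are higher.

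**Analysis.** CAE means and DES subscale means are compared by two-tailed independent t-tests. Feasibility and acceptability proportions, and EPDS and ALPHA detection, are compared by chi-square tests. Medical risk appears as a candidate predictor for secondary objective 3 (Table 1) and as a subgroup under Psychometric properties.

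**The concern.** There are two linked problems.

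First, the baseline tests cannot do what they are planned for. When a computer allocates at random, any difference in a characteristic fixed before allocation is due to chance, so the null hypothesis is already known to be true. Some of these items are also answered after the woman has used the assigned screening mode. A woman who has just screened on a tablet may rate her comfort with tablets differently, and self-reported mental health history or ACES might be affected too. A significant difference on such an item could be carry-over, chance, or both, yet the plan would read it as a failure of randomization.

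Second, setting is known for every woman before allocation and is, on the protocol's own account, strongly related to what the trial measures in its detection outcomes. Leaving it out of both the randomization and the between-arm tests gives up precision and leaves the detection result open to a chance difference in the mix of hospital and clinic women.

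**Working it through.** **1. The plan's own sample size.** Inputs (Table 2): p = 0.85, margin 0.05, 95% CI, 25% attrition. n = 0.85 × 0.15 × (1.96/0.05)² = 195.9, so 196. Then 196/0.75 = 261.3. The stated 261 per group (522 in total) reproduces and is used below. The abstract's 542 (271 per arm) would change the 8.6 points in step 4 only to 8.4.

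**2. Order of events.** Recruitment procedures, Procedures and Data collection procedures together give: consent, allocation, ALPHA/EPDS in the assigned mode, CAE and DES, baseline questionnaire. No section places the baseline questionnaire before allocation. Both arms answer it on the tablet, so only carry-over from the preceding ALPHA/EPDS mode can differ between arms.

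**3. What the baseline tests would show under correct randomization.** The number of tests is not stated. Assuming 15 independent tests at 0.05, 15 × 0.05 = 0.75 significant results are expected, and the chance of at least one is 1 − 0.95¹⁵ = 54%. For 20 tests it is 64%.

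**4. Chance imbalance in setting.** Intake is 50 clinic and 45 hospital women per month (Feasibility of achieving sample size), so the hospital share is q = 45/95 = 0.474, assuming equal participation.
- SD of the between-arm difference in hospital share = √(2 × 0.474 × 0.526/261) = 4.4 points.
- 95% range = 1.96 × 4.37 = ±8.6 points.
- The probability of a difference above 5 points is 25%, and above 10 points 2.2%.

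**5. Effect on EPDS detection.** The protocol gives no positivity by setting. Assume 10% in clinics and 30% on the unit, a ratio of three.
- Shift at the edge of the 95% range: 0.086 × 0.20 = 1.7 points.
- Overall positivity = 0.526 × 0.10 + 0.474 × 0.30 = 0.195; variance = 0.195 × 0.805 = 0.157.
- Standard error of the arm difference = √(2 × 0.157/261) = 3.5 points, so the shift is about half a standard error.
- Variance explained by setting = 0.474 × 0.526 × 0.20² / 0.157 = 0.0100/0.157 = 6.4%.

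Range over other assumptions with the same ratio:

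| Clinic / unit positivity | Shift at 8.6 points | Standard error | Variance explained |
|---|---|---|---|
| 10% / 30% | 1.7 | 3.5 | 6.4% |
| 13% / 39% | 2.2 | 3.8 | 8.9% |
| 20% / 60% | 3.4 | 4.3 | 16.8% |

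**6. Simulation** (20,000 trials, 522 women, simple 1:1 allocation; chi-square against a Cochran-Mantel-Haenszel test stratified by setting). Overall type I error was about 0.05 for both tests. Among trials in which the intervention arm held over 5 points more hospital women (about 13% of them), type I error of the unadjusted test was 0.068 (13%/39%) or 0.087 (20%/60%), while the stratified test stayed at about 0.05. For an assumed 10-point true difference, power rose from 0.705 to 0.738 (13%/39%) or from 0.635 to 0.710 (20%/60%).

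**The case against.** The case for leaving the plan alone has several parts.

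- **Simple randomization of about 522 women is valid.** This stands: overall type I error is about 0.05 without adjustment. A reader might infer that the planned tests are biased or invalid, and the calculations do not support that.
- **The gain is modest and rests on assumptions.** This stands too. At one SD of imbalance the shift is 4.4 × 0.20 = 0.9 points, about a quarter of a standard error. The threefold ratio is a literature figure on mental health problems, so it informs the detection outcomes only. Nothing in the protocol links setting to the CAE.
- **The trial does not hypothesise that mode alters the baseline items.** Correct. A reader might infer that it does, but Table 1 predicts effects on CAE and acceptability, EPDS and ALPHA positivity, DES scores, psychometrics and cost. It lists mental health history as a factor associated with acceptability. Carry-over is plausible for a few items and is an inference; age, parity and similar items are hardly affected.
- **Not every comparison is an unadjusted t or chi-square test.** Correct. Psychometric properties uses correlational and ROC analyses, with subgroups by medical risk. Neither that subgroup nor the candidate-predictor role adjusts the CAE, acceptability, detection or DES comparisons.
- **No arm comparison is planned to adjust for the late items.** Correct. The logistic models that include mental health history and ACES look for predictors. The risk of adjusting for a consequence of the arm would arise only if such adjustment were added later.
- **Moving the whole questionnaire before allocation has a cost.** Correct. Asking sensitive questions on the tablet first could prime women and weaken the paper-versus-tablet contrast in disclosure. Equal exposure in both arms does not remove that.

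**Conclusion.** The point holds as an improvement in design and analysis; it is not a flaw that invalidates the trial. The document itself fixes three things: the purpose of the baseline tests, the placing of the questionnaire after allocation and screening, and simple randomization followed by unadjusted between-arm tests. The baseline P-values cannot show whether randomization worked and, on mode-sensitive items, could mislead.

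For setting, the loss is precision and exposure to chance imbalance: up to about 1.7 points on EPDS detection at the edge of the 95% range, against a standard error of 3.5, with about 6% of variance removable. These figures assume 10% and 30% positivity and a 47% hospital share; the wider range tried gives 1.7 to 3.4 points and 6% to 17%. The size for the primary CAE outcome cannot be derived from the document.

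**What to change.** 1. **Adjust for setting** (clinic or antenatal unit) in the CAE, feasibility/acceptability, detection and DES comparisons: Mantel-Haenszel or logistic regression for proportions, a linear model for means. Setting is known for every woman before allocation, so the cost is one model term and this remains possible after recruitment has begun.
2. **Stratify the computer randomization by setting if recruitment has not started.** Trial status gives September 2013 as the start and the article appeared in January 2014, so this may no longer be open. Stratification needs restricted allocation within each stratum, for example concealed blocks of varying size; separate simple lists would not balance the arms.
3. **Replace the baseline tests with a descriptive table by arm**, and remove the stated aim of judging randomization by P-values. This costs nothing.
4. **Label the questionnaire as collected after allocation.** Do not use its mode-sensitive items as covariates in arm comparisons or as evidence about randomization.
5. **Optionally, collect neutral demographics before allocation.** This means re-ordering some tablet screens and adds a short delay before allocation. Mental health history and ACES can stay where they are, to avoid priming.
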